#### Anesthesia management

Preoperative: Informed consent will be signed preoperatively. Potential participants will be identified by reviewing the inpatient list or surgery schedule, and patients will be visited to sign the informed consent and baseline information will be collected. For patients included in CG group, a disposable glucose monitoring probe is placed and connected to the monitoring system 6 h prior to surgery.Intraoperative: reliable intravenous access will be established after the patient enters the operating room, and electrocardiograph, blood pressure, pulse oximetry, end-expiratory carbon dioxide, and bispectral index (BIS) monitoring will be routinely performed. After adequate preoxygenation, standardized induction of anesthesia is started with propofol or etomidate, sufentanil or fentanyl, rocuronium bromide, or *cis*-atracurium. The actual drug dose should be adjusted by a qualified anesthesiologist based on the patient’s circulatory changes and surgical tolerance. Intraoperative anesthesia is maintained using total intravenous anesthesia, inhalation anesthesia, or a combination of static and inhalation anesthesia to maintain a stable depth of anesthesia. All medications should be recorded in detail and the patient should be transferred to the ward or recovery room or intensive care unit (ICU) for observation after the surgery.Postoperative analgesia: After the surgery, patients routinely use a patient-controlled analgesic device with a recommended analgesic formulation of sufentanil 250 μg + ondansetron 20 mg + saline to 250 ml, with specific parameters of the analgesic pump adjusted according to the patient’s condition. With the regular postoperative analgesic dose, if the patient still has moderate or above postoperative pain (defined as: numerical rating scale ≥ 4/10), additional analgesic drugs can be added with the permission of the physician in charge, but the reason for administration and the type of drug administered should be recorded in detail.

#### Criteria for discontinuing or modifying allocated interventions {11b}

Interventions will be suspended in case of unintended or adverse events, or incomplete information collection that may has negative impact on the acquisition and interpretation of data, or in case of serious protocol deviations and implementation errors. Participating patients may withdraw from the study at any time and for any reason they wish, without consequence.

#### Strategies to improve adherence to interventions {11c}

For the participants in the intervention group, the alarm function of the CGM device will be turned on during LT. The device will continuously alert when the blood glucose value monitored by CGM is < 7.8 mmol/L or > 10.0 mmol/L, or the rate of change is > 1.67 mmol/(L∙min), in order to remind the investigator to reconfirm the blood glucose value using ABG test.

#### Relevant concomitant care permitted or prohibited during the trial {11d}

A conventional anesthetic management protocol is used intraoperatively. In the absence of clear indications, the control group should avoid two blood glucose monitoring intervals of less than 2 h. ABG testing in the intervention group should be performed only when the blood glucose value monitored by CGM is < 7.8 mmol/L or > 10.0 mmol/L, or the rate of change is > 1.67 mmol/(L- min).

#### Provisions for post-trial care {30}

No provisions or restrictions for post-trial care.

### Outcomes {12}

#### Primary outcomes

Intraoperative glucose coefficient of variation. In this study, the intraoperative coefficient of variation of blood glucose will be extracted from the CGM data for each participant (from the beginning of skin incision to the end of suture).

#### Secondary outcomes

This study intends to further assess the effectiveness of CGM-based intraoperative glucose management in LT by mean intraoperative glucose values, as well as rates of hypoglycemic events and hyperglycemic events. The accuracy of CGM for intraoperative glucose monitoring will be evaluated by overall clinical mean relative error and Clarke error grid analysis. The safety of CGM for intraoperative glucose monitoring will be evaluated by the incidence of severe adverse reactions (SAEs).

Additionally, this study intends to evaluate the prognostic improvement of patients with different glucose monitoring modalities by comparing the incidence of SSIs, other infections, postoperative liver function, and major adverse cardiovascular events (MACE) in the two groups at 3 months postoperatively.

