### Intervention description {11a}

#### Blood glucose management

Blood glucose monitoring

Intraoperative glucose monitoring is performed in both groups using CGM (Guardian RealTime, Medtronic, USA) in combination with arterial blood gas. A disposable glucose monitoring probe will be placed in the patient's upper arm by the investigator 6 h before surgery and connected to the monitoring system.

In the CG group, intraoperative ABG testing will be performed if the CGM value is < 6.1 mmol/L or > 10.0 mmol/L, or the rate of change of CGM value > 1.67 mmol/(L·min). Blood glucose adjustment will be performed according to the arterial blood glucose value.

In the G group, CGM monitoring results were blinded to patients and investigators. Intraoperative arterial blood gas checks will be performed every 2 h, and blood glucose adjustments will be made based on blood glucose results, and the frequency of blood gas tests will be adjusted as needed. CGM is used to record intraoperative glucose data only.2)Blood glucose management target: The intraoperative blood glucose management target is 7.8 ~ 10 mmol/L in both groups.3)Blood glucose-lowering measures: see Table 1 for the intraoperative glucose management measures for patients in both groups.

**Table 1 Tab1:** Blood glucose intervention

Perioperative target blood glucose: 7.8 ~ 10 mmol/L • If ABG-derived blood glucose > 10 mmol/L measured for the first time, start insulin infusion Insulin dose and mode of administration: • Loading dose: 0.1 U/kg, I.V Maintenance dose: (blood glucose value/5)U/h, infusion			
**Blood glucose (mmol/L)**	**If BG increased from previous measurement**	**BG decreased from prior measurement by ≤ 1.67 mmol/L**	**BG decreased from prior measurement by > 1.67 mmol/L**
**> 13.4**	Increase rate by 3U/h	Increase rate by 3U/h	No change in rate
**11.7 ~ 13.4**	Increase rate by 2U/h	Increase rate by 2U/h	No change in rate
**10.0 ~ 11.7**	Increase rate by 1U/h	Increase rate by 1U/h	No change in rate
**7.8 ~ 10.0**	No change in rate	No change in rate	No change in rate
**6.1 ~ 7.8**	No change in rate	Decrease rate by 50%	Hold insulin infusion
**5.5 ~ 6.1**	• Hold insulin infusion • Check BG every 2 h • Restart infusion if BG > 10 mmol/L		
**3.9 ~ 5.5**	• Hold insulin infusion • Check BG every 30 min until BG > 5.5 mmol/L, resume BG checks every 2 h • Restart infusion at 1/2 the prior infusion rate if BG > 10 mmol/L		

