#### Adverse event reporting and harms {22}

Treatment-related clinical adverse reactions including puncture site hematoma, infection, hypoglycemia, and hyperglycemia will be considered. The investigator should inform the participant of any emerging adverse events, and the participant should also report changes in condition truthfully in accordance with the protocol. The investigator should keep detailed records of all adverse events, including symptoms, time of presentation, duration, management measures, and effects, and evaluate their relevance to the study treatment. Investigators should be alert for serious adverse events (SAEs) such as severe hypoglycemia (< 3. 0 mmol/L), cardiac arrest due to dysglycemia, or death. Protecting the safety of the participants is the primary responsibility of the investigator. It should also be reported to the ethics committee, data monitoring committee, and relevant regulatory agencies, indicating the expectedness, severity, severity, and causality. DSMA regularly reviews study data and adherence to the protocol and makes recommendations regarding continuation, modification, or termination of the trial when necessary.

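### The stated CGM safety outcome counts only SAEs, a term given two meanings, so ordinary puncture-site reactions the protocol itself lists are recorded but not counted

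*Protocol article*

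**What the plan says.** Under Secondary outcomes the protocol names one measure of device safety: "The safety of CGM for intraoperative glucose monitoring will be evaluated by the incidence of severe adverse reactions (SAEs"). The Abbreviations list expands SAEs in the same way.

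Under Adverse event reporting and harms {22} the scope is wider: "Treatment-related clinical adverse reactions including puncture site hematoma, infection, hypoglycemia, and hyperglycemia will be considered". Recording is complete: "The investigator should keep detailed records of all adverse events, including symptoms, time of presentation, duration, management measures, and effects", with an assessment of how each event relates to study treatment. The same section gives SAE a different expansion and illustrates it: "serious adverse events (SAEs) such as severe hypoglycemia (< 3. 0 mmol/L), cardiac arrest due to dysglycemia, or death".

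On who wears the sensor, Blood glucose management states: "Intraoperative glucose monitoring is performed in both groups using CGM (Guardian RealTime, Medtronic, USA) in combination with arterial blood gas". For controls it adds: "CGM is used to record intraoperative glucose data only". Primary outcomes takes the coefficient of variation from each participant's CGM data. Study setting, however, describes control monitoring as blood gas alone, and Anesthesia management mentions probe placement for the CG group only.

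**The concern.** The protocol lists local reactions as harms to be considered and has them recorded, then defines the safety outcome for CGM by a class of events whose examples are all glycemic or fatal. A non-serious hematoma or infection at the sensor would appear in the adverse event record and nowhere in the outcome on which CGM safety is to be judged.

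The two meanings of SAE add to this. Severity is intensity, while seriousness concerns outcome or consequence. A reaction presumes a causal link; an event does not. In liver transplant recipients, where deaths unrelated to glucose monitoring can occur, counting severe reactions and counting serious events can give quite different totals.

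The trial sets out to study the feasibility as well as the effectiveness of CGM in major surgery (Trial design {8}). A statement about its safety should cover the local harms that the protocol has itself identified.

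**Working it through.** The protocol gives no safety rate, margin or power, so there is no stated figure to reproduce. The check compares sections and then sizes what the recorded data could show.

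**1. Which events enter the safety outcome**

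| Event | Recorded under {22}? | Among the SAE examples in {22}? | In a secondary outcome? |
|---|---|---|---|
| Puncture-site hematoma, not serious | Yes | No | No |
| Infection at the puncture site, not serious | Yes | No | Not named |
| Hypoglycemia, hyperglycemia | Yes | Only severe hypoglycemia | Yes, as event rates |
| Cardiac arrest from disturbed glucose, death | Yes | Yes | Yes, through SAEs |

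The infections named under Follow-up period are surgical site, abdominal, pulmonary and urinary tract. The first two rows are the gap.

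**2. Who is at risk of a sensor reaction**

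Blood glucose management and Primary outcomes imply sensors in both groups: 90 + 90 = 180 planned. Study setting and Anesthesia management read as the CG group only: 90. The first reading is better supported, because the primary outcome needs CGM data from everyone, but the text conflicts.

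**3. What a descriptive tabulation could show**

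Inputs: n = 90 or 180 (Sample size {14}). The rate p of sensor-site reactions is not in the document, so it is an assumption, taken here from 0.5% to 5%.

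Upper confidence limit when no event is seen:

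- One-sided 95%, 1 − 0.05^(1/n): n = 180 gives 1.65%; n = 90 gives 3.27%.
- Upper end of a two-sided exact 95% interval, 1 − 0.025^(1/n): n = 180 gives 2.03%; n = 90 gives 4.02%.

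Chance of at least one event, 1 − (1 − p)^n:

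| Assumed p | n = 90 | n = 180 |
|---|---|---|
| 0.5% | 36% | 59% |
| 1% | 60% | 84% |
| 2% | 84% | 97% |
| 5% | 99% | over 99.9% |

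For example, at 1%: 1 − 0.99^180 = 0.836 and 1 − 0.99^90 = 0.595.

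**4. What a comparison by arm could show**

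If both arms wear the same sensor at rate p, the expected difference in sensor-site reactions is p − p = 0 for any p. Such a comparison would address the effect of acting on the readings, not of wearing the device.

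**The case against.** The strongest reply is that the protocol already deals with these harms. The adverse event section says the local reactions will be considered and has all events documented and related to treatment. The SAE list is illustrative, so a serious site infection or hematoma could count. Hypoglycemic and hyperglycemic events are secondary outcomes in their own right. Tabulation of non-serious events is commonly left to an analysis plan, and the case report form and study schedule figure are not available here.

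Most of that stands, and it rules out several stronger readings that a reader might infer:

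- *That the trial cannot show the sensor's local harms.* The records will exist; the named outcome simply does not draw on them.
- *That safety rests on a comparison whose expected difference is zero.* The safety sentence specifies no test between arms; a pooled incidence is compatible with it.
- *That the listed reactions are purely sensor harms.* The text says puncture site, and both groups also have arterial blood sampling.
- *That there is nowhere to record a sensor-site infection.* The follow-up list names none, but the adverse event record would take one.
- *That pooling the arms halves the uncertainty.* This is so for the zero-event upper limit. In general, doubling n multiplies the standard error by 1/√2 = 0.71, a reduction of about 29%.
- *That the trial would declare CGM safe.* No criterion for such a conclusion is set.

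The reply does not remove the narrower point. Table layout can wait for an analysis plan, but which events make up the safety outcome is already stated under Outcomes {12}, and stated more narrowly than the harms listed under {22}. The two expansions of SAE are a contradiction within the document.

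**Conclusion.** The concern holds as a fault in the stated outcome, not as an inability of the trial to detect harm. Followed as written, non-serious hematoma or infection at the sensor site is recorded but not counted in the CGM safety outcome, and SAE has two meanings that yield different counts.

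The effect is confined to the safety conclusion; the primary outcome and its analysis are untouched. Counting the local reactions would allow a statement such as a one-sided 95% upper limit of 1.65% (180 wearers) or 3.27% (90 wearers) if none occurred. These limits assume that every planned participant in the relevant group has a sensor placed and is assessed for local reactions. The detection probabilities rest on assumed rates. The remark that an arm comparison could not isolate device harm holds only if controls wear the sensor, on which the sections must first be reconciled.

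**What to change.** 1. Under Secondary outcomes, add sensor-site hematoma and sensor-site infection of any severity to the CGM safety outcome. Report them descriptively over all participants with a sensor placed, with an exact 95% confidence interval.
2. Report serious adverse events by randomised arm, labelled as the safety of CGM-guided management.
3. Use one definition of SAE in Secondary outcomes, Adverse event reporting and harms {22}, and Abbreviations.
4. Reconcile Study setting and Anesthesia management with Blood glucose management and Primary outcomes on whether controls wear the sensor. This sets the denominator at about 180 or about 90.
5. Record the site of each local reaction, so that sensor reactions can be told apart from those at arterial sampling sites.

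The cost is revised wording, one more descriptive table, and noting the site on a record already required. No extra visits or procedures are needed.

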#### Concealment mechanism {16b}

Random numbers, serial numbers, and group numbers will be placed in opaque sealed envelopes. Each sealed envelope will be sequentially numbered and kept in a secure location until the study is completed. After participants have signed informed consent and passed the inclusion and exclusion criteria screening, the same investigator ([name]) will open the envelopes with the same serial number in order of enrollment and inform the anesthesiologist of the treatment assignment. Participants and study stuff will not be blinded to the treatment assignment. Only follow-up stuff will be masked to treatment assignment.

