### Assignment of interventions: blinding

#### Who will be blinded {17a}

Only judicial assessors of outcomes and data analysts will be blinded to the group assignment, whereas care providers and patients are not blinded.

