## Abbreviations

SSIs: Surgical site infections
LT: Liver transplantation
GV: Glycemic variability
CV%: Coefficient of variation
CGM: Continuous glucose monitor
NMA: National Medical Products Administration
ABG: Arterial blood gas
MELD: Model for end-stage liver disease
BIS: Bispectral index
ICU: Intensive care unit
SAEs: Severe adverse reactions
MACE: Major adverse cardiovascular events
BMI: Body mass index
HbA1C: Glycosylated hemoglobin
SVV: Stroke volume variation
CRF: Case report form (CRF)

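### The safety endpoint has two definitions under one abbreviation: severe adverse reactions in the outcomes, serious adverse events including death in the harms section

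*Protocol article*

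**What the plan says.** All references are to the protocol article.

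- **Secondary outcomes, under Outcomes {12}:** the safety of CGM is to be "evaluated by the incidence of severe adverse reactions (SAEs"). No other measure is named for safety.
- **Abbreviations:** "SAEs: Severe adverse reactions".
- **Adverse event reporting and harms {22}:** "Investigators should be alert for serious adverse events (SAEs) such as severe hypoglycemia (< 3. 0 mmol/L), cardiac arrest due to dysglycemia, or death". The same section opens with "Treatment-related clinical adverse reactions including puncture site hematoma, infection, hypoglycemia, and hyperglycemia will be considered". It has the investigator keep records of all adverse events and "evaluate their relevance to the study treatment". Causality is one of the attributes to be given when events are reported onward.
- **Blinding:** Concealment mechanism {16b} says "Participants and study stuff will not be blinded to the treatment assignment", but masks follow-up staff. Who will be blinded {17a} blinds outcome assessors and data analysts, "whereas care providers and patients are not blinded".
- **Criteria for removal from the trial:** these include death within 3 months of transplantation. Section {20c} puts all randomized participants in the main analyses.

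**The concern.** An analyst working from the outcomes section and one working from the harms section would build different safety tables. The terms differ in two ways. A reaction is an event judged to be caused by the treatment, and the harms section uses the word in that sense; an event needs no such judgement. Severe describes intensity, whereas serious describes consequence.

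The first difference matters more. Under the outcome wording, a death in either arm leaves the safety count once someone decides that it was unrelated to glucose management. After liver transplantation, attributing a death to the intraoperative glucose strategy is largely a matter of opinion. If the person deciding knows the arm, the count is open to bias in a trial whose care providers are not blinded.

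**Working it through.** The plan gives no expected rate of deaths or serious events, so there is nothing to recompute. The check is to apply each wording to the same events.

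| Event | Severe adverse reaction (Secondary outcomes, Abbreviations) | Serious adverse event (harms section {22}) |
|---|---|---|
| Death judged unrelated to glucose management | Not counted | Counted on the plain reading, since death is listed without a condition |
| Cardiac arrest judged not to stem from dysglycemia | Not counted | Undecided: the example is tied to dysglycemia, but the list is open |
| Glucose below 3.0 mmol/L | Counted if judged related and severe | Counted on a measured threshold |
| Intense sensor-site reaction without serious consequence | Counted | Not among the examples; the section mentions such reactions separately |

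The first row is the clear conflict. The third shows that a judgement is added even where the harms section relies on a measurement. The fourth shows that intensity versus seriousness changes the count independently of causality.

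**Who makes the judgement.** The harms section assigns it to the investigator. Study staff and care providers are unblinded ({16b}, {17a}). Follow-up staff and outcome assessors are masked (same sections). No section says whose classification feeds the safety endpoint. An unblinded call is the natural reading for events during surgery; for later events the text leaves it open.

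**Where else deaths are counted.** The Follow-up period list under {18a} collects all-cause mortality to 30 days and, within MACE, cardiovascular death; Secondary outcomes compares MACE at 3 months. A non-cardiovascular death between day 31 and day 90 that is judged unrelated would therefore fall in none of these counts under the outcome wording. The removal criterion for deaths within 3 months pulls in the same direction and conflicts with the all-randomized analysis in {20c}.

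**Sensor-site reactions.** Intervention description {11a} has CGM used in both groups, and Primary outcomes takes the coefficient of variation from each participant's CGM data. Anesthesia management describes probe placement for the CG group only. If both arms wear a sensor, a comparison between arms cannot show harm from the sensor itself.

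**The case against.** The strongest reply is that this is a slip of wording. The letters SAE fit serious adverse event and do not fit severe adverse reaction, the harms section is the only place that describes these events and their reporting, and the article has other slips of this kind. That is a likely explanation, and nothing shows that a related-only endpoint was chosen on purpose. But the reactions wording stands in the endpoint statement and again in the abbreviation list, so an analyst who follows the outcomes section literally would apply it.

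Three stronger readings are tempting, and the documents do not support them.

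- *The causality call is unblinded.* It may be, but the plan masks follow-up staff and outcome assessors and does not say who classifies events. What can be said is that masked classification is not specified for this endpoint.
- *The harms section gives a clean all-cause definition.* It does not: its cardiac-arrest example has a cause built in, and a reader could carry that condition over to death. Copying its term is not enough; the rule on attribution has to be written out.
- *Deaths called unrelated vanish from the trial.* Most would still be visible through 30-day all-cause mortality or cardiovascular death. The gap is limited to the later, non-cardiovascular deaths described above.

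**Conclusion.** The inconsistency is real and should be corrected. The only named safety endpoint has two definitions that count different events, and the one in the outcomes section adds a relatedness judgement by an investigator who may know the arm.

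Its size cannot be stated. A reader might want to assume a 90-day death rate and a number of attributed deaths and infer how far the safety result would move. The document supplies neither figure, and rates within one arm would not show a change in the comparison between arms. The conclusion rests on the text alone: the two expansions of the abbreviation, and the harms section's use of adverse reactions for treatment-related events.

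This is a secondary endpoint. The primary outcome and the sample size are not affected.

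**What to change.** 1. In Secondary outcomes and Abbreviations, replace severe adverse reactions with serious adverse events, as in the harms section.
2. State that these are counted in both arms regardless of attributed cause over the 90-day follow-up, deaths included, and give the start of the window so that intraoperative events fall inside it.
3. Reconcile this with the criterion that removes patients who die within 3 months, so that those deaths stay in the safety count.
4. Report events judged related on a separate line, and say who makes that judgement and whether that person is masked.
5. Reconcile Intervention description {11a} and Primary outcomes with Anesthesia management on which patients receive a sensor. If both arms do, report sensor-site reactions as one pooled rate over all sensor wearers.

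The cost is a few wording changes and an extra line or two in the safety table. The harms section already requires all adverse events to be recorded, with an assessment of relatedness. The small downside is a higher reported rate of serious adverse events, since it will include events due to the transplant itself in both arms.
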